## Abstract

Decision-making for the optimal management of traumatic knee injuries can be challenging. Clinical trials reveal only small differences between surgical and non-surgical approaches, while patient and clinician biases, as well as healthcare access issues, may also influence management. Little is known about the real-world healthcare pathways for patients with a knee injury, as well as the person- and/or healthcare-related factors that influence management strategies and outcomes. The Australian Knee Injury Inception Cohort Study (KIICS) aims to: (1) describe healthcare pathways following acute knee injury (including the timing and type of healthcare consultations); (2) identify patient- and/or healthcare-related predictors of management strategy (ie, surgical vs non-surgical); and (3) examine the long-term outcome of different injury types, healthcare pathways and management strategies. KIICS is a nationwide prospective longitudinal inception cohort study recruiting Australians who have sustained an acute knee injury within the previous 6 months that disrupted daily activities or sports and led to a healthcare consultation. Participants will complete online questionnaires at enrolment and at 6 months, 1, 2, 5 and 10 years post-injury. The data to be collected will include sociodemographic characteristics, knee injury history, the sequence of healthcare consultations and referral patterns, and management strategies (ie, surgical vs non-surgical). Patient-reported outcomes will include knee pain and instability, knee-related quality of life, patient-acceptable symptom state, health-related quality of life, mental health, fear of reinjury, return-to-sport status and activity level. Detailed statistical analysis plans will be developed to address the study’s key research questions, informing clinical practice, shared decision-making and healthcare policy.

WHAT IS ALREADY KNOWN ON THIS TOPICRates of traumatic knee injury and related surgery are rising globally.Rehabilitation with the option for surgery later, if required, leads to similar outcomes when compared with early surgery plus rehabilitation for common traumatic knee injuries such as acute anterior cruciate ligament rupture and meniscal tear.WHAT THIS STUDY ADDSFirst nationwide inception cohort study of traumatic knee injuries to capture the sequence of healthcare interactions and management decision-making (ie, healthcare pathway leading to surgical or non-surgical management).It will identify key factors (patient- and healthcare-related) influencing healthcare pathway and management strategy (ie, surgical or non-surgical management).It will provide 5- and 10-year follow-up data to assess long-term outcomes of various traumatic knee injuries, healthcare pathways and management strategies.HOW THIS STUDY MIGHT AFFECT RESEARCH, PRACTICE OR POLICYFindings will provide important data as to the multidisciplinary nature of care provided (or lack thereof) and how well care aligns with current best-practice guidelines.Data may influence referral pathway behaviour for optimal care and long-term outcomes for knee injuries, such as anterior cruciate ligament ruptures and meniscal tears.Results may lay the foundation for establishing a nationwide knee injury registry to comprehensively monitor knee injury outcomes and service provision, and inform future clinical guidelines for knee injury management.

## Introduction

 Rates of traumatic knee injuries, particularly ACL and meniscal tears, are rising globally.^1 2^ Australia has one of the world’s highest and fastest growing rates of ACL injuries and surgical ACL reconstruction (ACLR)—with ACLR rates rising more than 43% since 2000. An estimated 90% of young Australian adults who sustain an ACL injury undergo surgery.^3^ The highest rates of ACLR are seen in 20–24-year-old males at 283 procedures per 100 000 population.^4^ While ACL injuries are the focus of much research, other traumatic knee injuries, such as meniscal tears, medial and lateral collateral ligament (MCL, LCL) injuries, patellar dislocations and fractures, may also contribute significantly to long-term knee dysfunction and osteoarthritis (OA).

Despite advances in surgical and rehabilitation approaches, long-term outcomes following ACL and meniscal injuries remain suboptimal. 45% of patients do not return to their pre-injury level of sport.^5^ One in six and one in seven report persistent symptoms (eg, pain) up to 6 years post-ACLR^6^ and up to 2 years post-arthroscopic meniscus repair,^7^ respectively, contributing to reduced quality of life.^8^ On average, patients with a previous traumatic knee injury report worse knee health than their uninjured peers many years after their initial injury.^9^ In the long term, traumatic knee injuries confer a fourfold to sixfold increased risk of knee OA,^10^ and progression to total knee replacement is relatively quick, with sports-related knee injury more than doubling the hazard of subsequent knee replacement over 15 years.^11^ Given the rising incidence of traumatic knee injuries among young, active individuals and their long-term burden, these injuries represent an emerging public health concern with implications for both individual well-being and healthcare system sustainability.^12^

For ACL and meniscal tears, selecting the optimal management strategy can be challenging, particularly given longstanding misconceptions. Indeed, many patients^13^ believe that surgery is necessary for optimal recovery and return to sport, as well as reducing the risk of developing knee OA, which may be due to external influences (eg, clinicians,^14^ media). However, randomised controlled trials (RCTs) have challenged this belief, showing that long-term outcomes are largely similar following early surgery plus rehabilitation compared with rehabilitation alone, with the option of later surgery.^15^,^17^ Uptake of non-surgical, evidence-based rehabilitation remains low—likely due to entrenched beliefs, lack of access and systemic barriers.^18^ Choosing ACLR as a first-line intervention for all may not be cost-effective.^19^ The direct costs of ACL surgery and rehabilitation in Australia are ~$A15 000 per person, and projected to exceed $A314 million annually by 2030.^20^ Understanding the factors that influence patients’ uptake of different management strategies and how they navigate the healthcare system is essential to inform strategies to assist decision-making.

Little is known about what drives the healthcare pathways taken by individuals with acute knee injuries, including which providers they see, in what order, and how these sequences influence management strategy (eg, surgical vs non-surgical). Research on other musculoskeletal conditions, such as low back pain, suggests that the initial healthcare encounter and referral patterns significantly impact the quality of care and patient health outcomes.^21^ Similar patterns may exist in knee injury care, with current evidence indicating large variations in healthcare pathways for ACL injuries in the UK.^22^ Large-scale registries, such as those in Scandinavia,^23 24^ have provided valuable insights into ACL injury management, including predictors of clinical outcomes and graft failure. However, these registries focus on surgically managed patients, and no equivalent registry or national longitudinal cohort exists in Australia. Real-world longitudinal data comparing surgical and non-surgical pathways outside the context of RCTs are lacking in Australia, although such research has been conducted in other countries.^25^ It is critical to understand the effectiveness of various management strategies, including multidisciplinary or stepped care pathways.

The Australian Knee Injury Inception Cohort Study (KIICS) aims to: 1) describe healthcare pathways following acute knee injury (including the timing and type of healthcare consultations) (figure 1); 2) identify patient- and/or healthcare-related predictors of management strategy (ie, surgical vs non-surgical); 3) examine the long-term outcome of different injury types, healthcare pathways and management strategies.

**Figure 1 F1:**
[figure not shown]
Examples of healthcare pathways for Australians sustaining a knee injury.

## Methods and analysis

### Study design

This study is a nationwide longitudinal prospective inception cohort study that will recruit Australian residents who sustained a self-reported traumatic knee injury in the previous 6 months. Data will be collected online through the Research Electronic Data Capture (REDCap; Vanderbilt University, Tennessee, USA) web-based survey system hosted on a secure server at La Trobe University.

### Participants

Australian residents of any age who have sustained a traumatic knee injury in the previous 6 months are eligible. A traumatic knee injury is defined as a knee injury of sudden onset that is severe enough to interrupt daily life, work, school and/or sport activities for more than 24 hours, resulting in contact with the healthcare system (eg, for imaging, diagnosis and/or management). Australian residents are defined as those living in Australia at the time of their knee injury and throughout most of their healthcare pathway. The aim is to recruit at least 1000 participants.

### Recruitment procedure

Recruitment commenced in August 2024 and will continue until 2027. Enrolment will occur nationwide, on an opt-in basis. Recruitment initially commenced in community settings, with subsequent involvement from public hospitals that will recruit from public healthcare settings (eg, emergency department, outpatient orthopaedic/physiotherapy clinics).

In community settings, participants will be recruited through: direct referral from treating healthcare providers; posters and flyers at healthcare clinics (eg, sports medicine, physiotherapy, general practitioner, radiology, orthopaedic) and community organisations (eg, sports clubs, gyms, universities) who agreed to promote the study; posters and flyers on social media, community notice boards and community newsletters.

In public healthcare settings, participants will be recruited through: direct referral from treating healthcare providers via study invitation sent to patients who were treated for an acute knee injury in the past 6 months; posters and flyers in emergency department waiting rooms and relevant outpatient clinics.

All recruitment materials will include a weblink and QR code to the study home page (www.kneeinjurystudy.com.au), where potential participants can register their interest, provide consent and complete the screening and baseline questionnaires if deemed eligible. Individuals interested in participating in the study will be automatically screened for eligibility within REDCap by answering six questions (figure 2). Eligible participants will be directed to the online patient information and consent form. Once participants have provided consent (via e-signature), they will be directed to the baseline questionnaire. For participants under 18 years of age, parental/guardian consent (e-signature) will be required.

**Figure 2 F2:**
[figure not shown]
Eligibility screening questions. GP, general practitioner.

### Data collection procedure

Data will be collected at baseline (on initial enrolment in the study) and at 6 months, 1, 2, 5 and 10 years after the initial injury. For each follow-up, participants will receive an email with a link to the online questionnaire. To support retention and address potential issues, such as participants changing their email addresses during the study, reminders will be sent via email, phone call and text message. Informed by our consumer advisory group (CAG), data collection will be kept to a minimum at each time point (less than 5–10 min) to minimise participant burden and encourage retention. For this reason, some questionnaires include only specific subscales and single-item scores for certain constructs (online supplemental table 1) provides detailed information about the questionnaires. If any questionnaire is incomplete or further clarification is required regarding participant responses, a member of the research team will telephone participants to follow-up or seek clarification.

### Outcomes

#### Baseline demographic, injury characteristics and outcome expectations

Demographic characteristics will include age, sex, gender and current residential postcode. The postcode will be used to classify geographic location (eg, metropolitan vs regional, state of residence) using the Australian Statistical Geography Standard and infer socioeconomic status (via linkage with the Socio-Economic Indexes for Areas index). Details regarding current knee injury will include the involved side (index knee), the Australian state and setting (eg, sport, work, other) where the injury occurred, diagnosis and how it was confirmed (eg, self-reported, clinician-diagnosed or imaging-confirmed), as well as the patient’s patient preference for management options. For those who have not undergone post-injury surgery at baseline, management preference will be assessed with the question ‘If you were asked right now to choose surgery or rehabilitation without surgery, which option would most accurately represent your answer?’ with five response options ranging from ‘Strong preference for surgery’ to ‘Strong preference for rehabilitation without surgery’. In addition to self-report, knee injury diagnosis will be confirmed via imaging reports (if imaging has been performed) from clinical services. With participant consent, a member of the research team will contact the clinic or imaging provider where the participant reported having their imaging performed, to request a copy of the report. Information about prior knee injuries (eg, side involved, diagnosis) will also be recorded. Participants’ recovery expectations will also be assessed with the question ‘Overall, how do you expect your knee to be 1 year after your injury?*’* with responses recorded on a 7-point Likert scale (range: 1=very much worse, 7=completely recovered) which corresponds to the Global Rating of Change scale used to assess self-perceived change in knee status (table 1).

**Table 1 T1:** Overview of outcomes

	Baseline	6 months	1 year	2 years	5 years	10 years
Demographic and knee injury characteristics						
Age, sex, gender, postcode	√					
Current and prior knee injury details	√					
Recovery expectations	√					
Self-reported outcomes						
Healthcare pathway Private insurance cover and how treatment was paid for Healthcare provider seen, sequence and timing Referral patterns Imaging acquisition Surgical procedures Rehabilitation participation		√	√			
Patient acceptable symptom state	√	√	√	√	√	√
Health-related quality of life (EQ-5D-5L)	√	√	√	√	√	√
Mental health (100-point VAS)	√	√	√	√	√	√
Knee pain (100-point VAS)	√	√	√	√	√	√
Knee instability (100-point VAS)	√	√	√	√	√	√
Activity level (TAS)	√	√	√	√	√	√
New/reinjury occurrence and details		√	√	√	√	√
Global rating of change		√	√	√	√	√
Function in sport and recreation (KOOS-Sport/Rec)		√	√	√	√	√
Knee-related quality of life (KOOS-QoL)		√	√	√	√	√
Fear of reinjury (100-point VAS)		√	√	√	√	√
Surgery occurrence and details				√	√	√

KOOS, Knee injury and Osteoarthritis Outcome Score; TAS, Tegner Activity Scale; VAS, visual analogue scale.

#### Healthcare pathway

Each participant’s healthcare pathway following knee injury will be documented via self-report regarding:

Use of private health insurance vs public healthcare, and how knee injury treatments (eg, surgery, rehabilitation) were funded;Private health insurance paid some/all of the treatment cost; sports injury insurance covered some/all of the treatment cost; my employer/work cover (worker compensation insurance) covered some/all of the treatment cost; I paid all treatment costs out of pocket (no insurance); treatment was provided through the public health system at no/little cost to me; I don’t remember; other (if other, free text to provide details).Every type of unique healthcare provider consulted for their knee injury, in what sequence and time post-injury consulted;Type: emergency department staff, general practitioner, sports physician, physiotherapist, orthopaedic surgeon, other (if other, free text to provide details).Sequence: First, second, third, fourth, fifth healthcare provider consultedTiming: within 1 week post-injury, >1 to 2 weeks post-injury, >2 to 4 weeks post-injury, >1 to 2 months post-injury, >2 to 3 months post-injury, >3 to 6 months post-injury, >6 months post-injury.Who referred them (general practitioner, emergency department staff or sports physician if applicable) and where they were referred to (imaging, general practitioner, sports physician, physiotherapist, orthopaedic surgeon, outpatient hospital clinic, other (if other, free text to provide details)).Imaging acquisition details (eg, type of imaging (X-ray, MRI, CT, ultrasound) and clinic where it was acquired) and surgical procedure details (eg, type, when, graft used if ACLR) if applicable.Rehabilitation professional involvement, and if so, how long (eg, length of follow-up and number of sessions since injury).

#### Patient satisfaction

Patient satisfaction with knee health will be assessed using the patient acceptable symptom state (PASS), which is a single question with a yes/no response: ‘Taking into account your level of pain and function, if you were to remain for the next few months as you are today, would you consider that your current state is satisfactory?’. The PASS is frequently used to assess symptom status in conjunction with traditional patient-reported outcome measures. It has shown good content validity and good to excellent reliability (intra-class correlation coefficient=0.8, online supplemental table 1) in the context of knee injuries.

#### Health-related quality of life

Health-related quality of life will be assessed with the EQ-5D-5L instrument and overall rating of health on a visual analogue scale (EQ-VAS). The instrument covers five domains: mobility, self-care, usual activities, pain or discomfort, and anxiety or depression. The presence and severity of problems on each domain are rated on a 5-point Likert scale (no problems, slight, moderate, severe, extreme problems). Responses are used to generate a health profile with 3125 possible health states defined by combining one level from each dimension, ranging from 11 111 (full health) to 55 555 (worst health).^26^ These health states are converted into a single index ‘utility’ score using an Australian value set, with possible values ranging from −0.30 (worse than death) to 1.0 (perfect health).^27^ The EQ-VAS component asks patients to rate their perceived health today from 0 (worst imaginable health) to 100 (best imaginable health).^26^ While most validation studies of the EQ-5D in knee injury populations have focused on patients with OA, it is widely used in large knee injury registries, including Scandinavian registries, such as the Swedish National Knee Ligament Registry, supporting its utility for comparison across studies and populations.

#### Mental health

Mental health status will be assessed with the question, ‘In the last week, how has your knee injury impacted your mental health?’. Responses will be recorded on a 100-point VAS (0=no impact on mental health, 100=extreme impact on mental health). VAS has demonstrated validity for assessing constructs like pain and emotional distress (online supplemental table 1), and adapting them for mental health outcomes related to knee injuries is an accepted and practical approach.

#### Knee pain and instability

Knee pain will be assessed with the question ‘In the last week, on average, how painful was your knee?’. Responses will be recorded on a 100-point VAS (0=no pain, 100=worst pain). Knee instability is assessed with two questions: (1) ‘During the last week (or since your injury if your injury was less than 1 week ago), how stable is your knee in everyday situations?’; and () ‘During the last week (or since your injury if your injury was less than 1 week ago), how stable is your knee when you do, or try to do, rehabilitation training, recreational activities or sports activities?’. Responses to each instability question will be recorded on a 100-point VAS (0=no instability, 100=worst possible instability).

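### The baseline knee-pain item has no 'since injury' alternative for injuries under 1 week old, although both instability items beside it do, so its meaning is unclear in the earliest enrollers

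*Protocol article*

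**What the plan says.** In the protocol article, Knee pain and instability, the pain item reads "In the last week, on average, how painful was your knee", answered on a 0 to 100 visual analogue scale. It offers no other recall window.

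The first instability item in that section reads "During the last week (or since your injury if your injury was less than 1 week ago), how stable is your knee in everyday situations". The second, on training and sport, opens with the same bracket. Under Mental health, the item reads "In the last week, how has your knee injury impacted your mental health", also without the bracket.

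Four other places decide whether the case can arise:

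- Participants: "Australian residents of any age who have sustained a traumatic knee injury in the previous 6 months are eligible". No minimum time since injury is given. The injury must be "severe enough to interrupt daily life, work, school and/or sport activities for more than 24 hours" and must have led to healthcare contact.
- Recruitment procedure: one public-hospital route is "posters and flyers in emergency department waiting rooms and relevant outpatient clinics". Recruitment materials carry a weblink and QR code to the page where people screen, consent and complete baseline.
- Data collection procedure: baseline is completed on enrolment, while follow-ups are timed from the injury.
- Table 1: knee pain is collected at baseline and at every follow-up.

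**The concern.** A one-week average has a clear meaning only if the whole week lies after the injury. For someone injured two days ago, most of that week precedes the injury. The instability items deal with this by switching the window; the pain item does not. The bracket shows that the authors expected some respondents to be inside their first week, and the same people answer the pain item.

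At stake is the usability of baseline pain in the earliest enrollers. A literal reading gives a score that is too low, and an informal reading gives the pain since injury. The two kinds of answer cannot be told apart afterwards. Within one person, baseline pain and baseline instability may also cover different periods. Any analysis that uses baseline pain, or change in pain from baseline, takes on this ambiguity for that subgroup.

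**Working it through.** The article states no figure on this point, so there is none to reproduce. The check compares the items and then sizes what the wording invites.

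**Can it occur?** The definition requires more than 24 hours of interrupted activity plus a healthcare contact, so enrolment on days 2 to 6 is possible. Baseline is completed at enrolment and includes pain. The Healthcare pathway section also has a first-week category for the timing of consultations, so care that early is expected.

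**Effect on one score.** Let P be mean pain since injury, B mean pain on the days before it, and k the days since injury (k < 7). A literal respondent reports

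reported = (k/7) × P + (1 − k/7) × B,

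so the shortfall is (1 − k/7) × (P − B). B is not collected. Taking B = 0 (an assumption) gives reported = P × k/7. P is also assumed, so a range is shown:

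| Day k | k/7 | P = 40 | P = 60 | P = 70 | P = 80 |
|---|---|---|---|---|---|
| 2 | 0.29 | 11.4 | 17.1 | 20 | 22.9 |
| 3 | 0.43 | 17.1 | 25.7 | 30 | 34.3 |
| 4 | 0.57 | 22.9 | 34.3 | 40 | 45.7 |
| 5 | 0.71 | 28.6 | 42.9 | 50 | 57.1 |
| 6 | 0.86 | 34.3 | 51.4 | 60 | 68.6 |

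At P = 60 the shortfall runs from 42.9 points at day 2 to 8.6 at day 6. With the bracket added, the factor is 1 on every day and the report equals P.

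**Effect on the cohort mean.** Let s be the share enrolled under 7 days after injury, which the article does not give. With enrolment spread evenly over days 2 to 6 (assumed), the mean of k/7 is (2+3+4+5+6)/(5 × 7) = 4/7 = 0.571. If everyone in the group answers literally,

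shift = −s × P × (1 − 4/7).

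At P = 60:

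- s = 1%: −0.01 × 60 × 3/7 = −0.3
- s = 5%: −0.05 × 60 × 3/7 = −1.3
- s = 10%: −0.10 × 60 × 3/7 = −2.6
- s = 20%: −0.20 × 60 × 3/7 = −5.1

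Against the target of at least 1000 participants, shares of 5% and 10% mean 50 and 100 scores exposed to the ambiguity. That is not 50 to 100 scores known to be wrong.

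**Which measurements are untouched?** The scheduled follow-ups start at 6 months after injury, so a one-week window there cannot reach back before the injury.

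**The case against.** The strongest reply is that the bias is assumed, not shown. People answering a knee-injury survey two days after the event may simply rate their pain since the injury. The days before it need not have been pain-free either, since participants may have had earlier knee injuries. Both points stand. They reduce the expected shortfall, but they leave the score with an undefined window in this group.

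A second reply is that online supplemental table 1, which is not shown, may contain fuller instructions. That is possible. However, all three items are printed as verbatim questions and the bracket is printed twice, so condensation for the journal is an unlikely explanation.

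A reader might infer four stronger things, none of which the document supports:

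- That the models for Aims 2 and 3 are biased. The Statistical analyses section refers only to relevant confounders and baseline characteristics and leaves the detail to specific plans. It does not name baseline pain as a predictor or covariate.
- That the error is tied to emergency-department recruitment, and so to the pathway under study. A person reading a waiting-room poster within a day of injury does not yet meet the 24-hour criterion. Hospital invitations go to patients treated at any time in the past 6 months. The mix of early enrollers is unknown.
- That the most acute participants would appear among the least painful. No pain distribution is given for anyone, so there is nothing to rank them against.
- That the mental-health item shares the fault. It asks about the impact of the injury and requests no average, so days before the injury hardly dilute it.

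**Conclusion.** The point holds as an inconsistency of wording with a limited reach. The pain item lacks a clause that the authors thought necessary for the two items beside it, and the design allows the situation that the clause was written for.

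For a literal respondent with no pain before the injury, the understatement is large: 50 points at day 2 if the post-injury mean is 70. Across the cohort it is probably small, about 1 to 3 points at an assumed 5–10% share and a mean of 60. Those figures suppose that everyone in the group answers literally and that enrolment is spread evenly over days 2 to 6. Answers that cover only the days since injury would reduce them. The first-week share is the main unknown.

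The defect affects baseline pain, and change from it, in participants enrolled under 7 days after injury. It does not affect the follow-up scores, and it does not threaten the study's aims. It is worth correcting because recruitment is planned to continue to December 2027 and the remedy is simple.

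**What to change.** Add the bracket from the instability items, "or since your injury if your injury was less than 1 week ago", to the pain item for the rest of recruitment, and record the date of the change.

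Flag every baseline pain score collected under the present wording within 7 days of injury. Follow-ups are timed from the injury, so the interval from injury to enrolment should be obtainable. Wherever baseline pain or change from baseline is used, repeat the analysis without the flagged scores. Report how many are flagged, which replaces the assumed share above with a known one.

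The cost is one item edit and one derived variable, with no added burden for participants. The small downside is a change of wording part-way through recruitment. It alters the question only for people in their first week, and the flag identifies those who answered before it. Adding the bracket to the mental-health item is optional, for consistency only.
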